### Data collection

During the annual visits, various study procedures will be conducted. Each centre in which the study visits take place (the “measurement centres”) has a dedicated team consisting of one or two research nurses, and one or two p that execute all study-related procedures. All study personnel will be trained in the study requirements and study procedures. Standard Operating Procedures (SOPs) will be provided to all study sites to enhance data quality and reduce variability in measurements as much as possible.

Parents will be instructed that their children should refrain from eating, brushing teeth, using inhalation medication, and moderate to severe exercise as much as possible within 60 min prior to the visit. Drinking of water is allowed prior to the tests. Prior to the annual visits, electronic questionnaires will be sent to the parents. In the RCT study group, a subset of these questionnaires will also be sent at three monthly intervals. The parameters that are measured are listed in Fig. 2.

A web-based study management system Ldot (https://nl.ldot.nl/) will be used to monitor the study logistics and guard the process of the research project. Ldot enhances participant retention by sending both automatically generated reminders for study personnel to contact patients, and automatically generated reminders to study participants to attend planned visits (both by e-mail and SMS messages). Also, periodic communications via newsletters and a website will be provided to parents, recruiting doctors, and treating doctors of participating patients.

### Volatile Organic Compounds

*Breath collection:* Breath samples will be collected by using a tailored breath sampling system for children developed by our department (Fig. 4). The children breathe tidally and without resistance through a silicone oro-(mouth) mask (Hans Rudolph, Inc., Kansas, USA), separating nasal and bronchial expired air, and connected to a Y-shaped, non-rebreathing two-way valve system (Hans Rudolph, Inc., Kansas, USA) [24]. At the inhalation port of the two-way valve, a VOC-filter (Combined filter A2B2P3, Honeywell, United States) is attached. This ensures inhaling environmental air free from exogenous VOCs. On the expiratory port of the valve a custom made 3-L polycarbonate bag (Tedlar® bag, samplebags.eu, The Netherlands) will be connected to collect the exhaled breath. The child will first be asked to breathe tidally for 3 min to ensure that the entire lung capacity is refreshed with environmental-VOC-free air. After 3 min the sampling bag will be attached to the exhalation port. After the bag is filled up to a maximum of 80%, the bag will be disconnected from the sampling device.

**Fig. 4 Fig4:**
[figure not shown]
Breath collection in a child using a tailored breath sampling system (see insert)

*SIFT-MS analysis:* the sampling bag will be connected to the Syft Voice 200 Ultra (Syft technologies, Christchurch, New Zealand) for SIFT-MS analysis of the breath. The instrument will be applied in full spectral mass scan mode in the mass-to-charge ratio (m/z) range of 15–250 amu for all three precursor ions (H3O^+^, NO^+^, O2^+^). Three acquisition repeats will be performed in a single run and the full scan data (ion counts per second) will be averaged over the three repeats for each m/z value. The SIFT-MS measurement uses approximately 60 ml of exhaled breath.

*GC-tof–MS analysis* the remaining breath in the sampling bag will be emptied across a stainless steel, two-bed sorption tube filled with Carbograph 1 TD/Carbopack™ X (Markes International, Llantrisant, UK) for rapid adsorption and stabilisation of volatile compounds. The tubes are airtight capped and stored at 4 °C until analysis. During the analysis, VOCs are first released from the tube using thermal desorption (Unity desorption unit; Markes International) at 270 degrees Celsius. In the next step, 25% of the mixture of vapour is loaded onto a cold (5 °C) sorption trap, while the remaining 75% of the mixture is recollected into an identical sample tube. The vapour mixture was then reloaded from trap into the gas chromatography time-of-flight mass spectrometry (Tempus Plus; ThermoFischer Scientific) (GC-tof–MS) analysis. The temperature of the GC was programmed as follows: first 40 °C for 5 min then it was increased by 10 °C every minute until 270 °C is reached. This temperature is maintained for 5 min. Electron ionisation at 70 eV was used with 5 Hz scanning rate over a range of m/z 35–350 [36]. The pre-processing of the raw GC-*tof*–MS spectra consists of noise removal, baseline correction, alignment, and peak detection. Thereafter, complementary compounds in different samples are linked, based on similarity of retention times and mass spectra. The area under the peak will be calculated for each compound. To make the spectra comparable, normalisation to the total area will be performed [37].

### Lung function

*Airway resistance test:* the airway resistance will be measured annually by means of the TremoFlo C-100™(Thorasys, Montreal, Canada) using the flow-oscillation technique (http://thorasys.com). The children will sit upright with their head in a neutral position and the researcher standing behind them to manually support the cheeks to minimise the upper airway shunt. The child will be asked to breathe quietly with the mouthpiece into his or her mouth, while making a seal with the lips around the mouthpiece and wearing a nose clip. The measurements will be repeated until at least three, artefact free measurements are completed. Thereafter, 300 µg of salbutamol will be inhaled via the Aerochamber®. After 15 min, the airway resistance measurements are repeated to assess the reversibility to a beta-2 agonist.

*Spirometry, bronchial NO and bronchial hyperresponsiveness:* additional lung function tests are performed during the final visit at age six years in order to make a definite asthma diagnosis in all participating children. These tests are performed and selected according to the ERS clinical practice guidelines for the diagnosis of asthma in children [38]. Spirometry and bronchodilator reversibility (BDR) testing is performed in which the highest forced expiratory volume in one second (FEV1), forced vital capacity (FVC), and maximal expiratory flow at 50% FVC (MEF50) of three technically satisfactory MEFV curves will be used for analysis. Also, in all children the fraction of exhaled nitric oxide (FeNO) will be measured with an online single breath technique with constant expiratory flow (NIOX VERO ®, Circassia AB, Oxford, UK). The Fractional exhaled NO (FeNO) value will be expressed as parts per billion. Only in a subset of patients in which a conclusive asthma diagnosis cannot be made based on spirometry, BDR and FeNO, a direct bronchial challenge test will be performed by administrating aerosols of methacholine.

### Microbiome

*Nasopharyngeal swab:* a nasopharyngeal swab will be taken at the age of 5 years. A sterile nylon flocked swab (FLOQSwabs®, COPAN, CA, USA) will be used. An aliquot of these swabs will be stored in Universal Transport Medium (UTM) at -80°C until used for determination of the microbiota of the lower airways.

*Faecal sample:* faecal samples of the children will be collected at baseline, at the age of 5 years and at the age of 6 years. These samples will be stored at -80°C and eventually used for microbiome analysis.

### Buccal swab

Isohelix Buccal swabs with RapiDri™ pouch will be used to sample buccal cells for isolating DNA at the baseline visit. The extracted DNA is used to study gene polymorphisms in selected candidate genes. The inclusion of genes for SNP analysis is based on the following criteria: association with asthma based on biomedical literature, a functional difference between the variant allele and the wild-type allele, and a minor allele frequency of at least 5% in the (asthmatic) population.

### Nasal epithelial brush

Nasal epithelial cells will be collected at the baseline visit by brushing nylon flocked swabs (FLOQSwabs®, COPAN, CA, USA) against the lateral side of the inferior turbinate of both nostrils. Two swabs will be transferred into sterile National Lab Cryovials, and two swabs will be transferred into sterile National Lab Cryovials filled with RNAlater™ stabilisation solution. All cryovials will be stored at -80°C until DNA and RNA extraction and subsequent determination of DNA methylation and RNA-sequencing.

### Venous blood sample

Six millilitres of venous blood will be sampled at baseline visit and at the end visit. One to two hours prior to the blood puncture, lidocaine 1% gel with 4 × 4 cm plaster will be applied. This blood will be used for.allergy testing: total immunoglobulin E (IgE) and determination of specific IgE antibodies to inhalant allergens (ImmunoCAP allergens gx3 (grass pollen), tx9 (tree pollen), wx3 (weed pollen), mx1 (moulds), d1 (house dust mite), e1 (cat dander), e5 (dog dander) (Phadiatop test; Phadia, Uppsala, Sweden)white blood cell count and absolute number of eosinophils will be determinedleukocyte subset analysis by flow cytometry: Extended phenotyping will be performed to evaluate B-cell maturation and differentiation (CD19, CD27, CD38, and IgD), and T-cell maturation and differentiation (CD3, CD4, CD8, CD28, CD45RA and CD127). These panels enable the distinction of pro- and anti-inflammatory lymphocyte subsets, the degree of memory formation as a marker for pathogen exposure, and early senescence. In addition, monocyte subsets (classical and non-classical) and dendritic cell subsets (myeloid and plasmacytoid dendritic cells) will be evaluated (CD11c, CD14, CD16, CD123, HLA-Dr, BDCA-2, and BDCA-3)isolation of peripheral blood mononuclear cells (PBMC’s): PBMC’s will be stored in liquid nitrogen for in vitro activation with distinct stimuli followed by analyses of the produced cytokine repertoire.isolation of eosinophils: In a subset of children (80 children with wheeze, 40 healthy controls) peripheral blood eosinophils will be isolated by FACS sorting. Blood eosinophils will be isolated from 2 ml of EDTA blood using an adapted FACS sorting strategy based on Mori et al. within 24 h of blood sampling, sorting Siglec8 + and CD193 + cells [39]. From sorted eosinophils, we will isolate DNA with the DNeasy blood and tissue kit (Qiagen, Venlo, the Netherlands) and investigate DNA-methylation using the Infinium Human Methylation EPIC Bead Chip array (Illumina, San Diego, USA).whole transcriptome RNA sequencing for gene expression of markers of inflammation and oxidative stress. One millilitre of venous blood will be transferred into sterile National Lab Cryovials. Invitrogen™ RNA*later*™ Stabilization Solution will be added to ensure immediate RNase inactivation and RNA stabilization within cells. All cryovials will be stored at -80°C until RNA extraction and subsequent RNA-sequencing.

### API and modified API (mAPI)

The API and mAPI (based on parental asthma, eczema, allergic rhinitis, wheezing apart from colds, and atopy) will be assessed at baseline [22].

### Questionnaires

Parents will be asked to complete several questionnaires during the study to assess asthma control, quality of life, and utilisation of health care and societal resources [40–42]. The questionnaires will be provided as e-version and will be sent to the parents two weeks before the annual clinical visits. Two questionnaires will be sent at a three-monthly interval: the questionnaires on asthma control (TRACK) and on utilisation of health care and societal resources.

*TRACK* Parents will be asked to complete the TRACK questionnaire at a 3-month interval. The TRACK questionnaire is a validated questionnaire on asthma control specifically developed for use in this age group, independent of the diagnosis. A score of 80 or more is defined as well controlled disease. The TRACK score is sensitive and reliable, and an increase of 10 points was found to be the ‘minimally important difference’ [43].

*ISAAC questionnaire (Core Questionnaire and Environmental Questionnaire)* The Core Questionnaire and the Environmental Questionnaire have been developed by the ISAAC steering Committee [44]. This questionnaire is used in this study to assess asthma, allergic rhinoconjunctivitis and eczema in all participants and to assess a variety of environmental factors.

*EQ-5D-Y (proxy version)* The EQ-5D-Y questionnaire is a validated child-friendly version of the EQ-5D on quality of life that comprises the following five dimensions with three answer levels (“no problems,” “some problems,” and “a lot of problems”): mobility, looking after myself, doing usual activities, having pain or discomfort and feeling worried, sad or unhappy. It also includes a visual analogue scale (VAS), which gives an overall assessment of the child’s health status in a scale from 0 (worst imaginable health state) to 100 (best imaginable health state). In the proxy version, the caregiver is asked to rate the child’s health-related quality of life (HRQoL). The EQ-5D-Y proxy-version has been tested in children as from 4 years of age [45], which revealed that some domains (e.g. self-care) were sometimes perceived by the parents as not suitable to young children. However, no alternative preference-based measure is currently available or has a validated proxy-version for use in preschool children.

*EQ-5D-5L* Quality of life of one of the parents will be assessed annually by the Eq-5D-5L [46]. The EQ-5D-5L comprises the same dimensions as the above mentioned EQ-5D-5L, but each dimensions has 5 levels (no problems, slight problems, moderate problems, severe problems and extreme problems). It also includes a vertical visual analogue scale to record the parents’ self-rated health.

*TAPQOL* The TAPQOL measures parent’s perceptions of HRQoL in preschool children. The questionnaire was developed for children between 9 months and 6 years old. The TAPQOL will be completed by one of the parents at baseline, and at 1 and 2 years of follow-up [42].

*Utilisation of health care and societal resources* a self-composed questionnaire to assess the number of days the child is not able to go to school/day-care, the number of days the parents are not able to work, the resource use within health care (control visits, emergency visits, hospital admission, visits to the doctor, lung function tests and other diagnostic procedures, medication) and ‘outside health care’ (over the-counter medication). This questionnaire will be completed at 3 months intervals by parents.

### Cost-effectiveness

Cost-effectiveness will be calculated as the incremental costs per child with well-controlled disease (based on the TRACK questionnaire) and incremental costs per quality-adjusted life year (QALY) (based onEQ-5-DY).

### Pharmacotherapy

Use of asthma medication and antibiotics will be continually registered: drugs, dosage, and period of use. Parents will be asked to register this using the app “Qdot studies” developed by Maastricht University. This app is specifically designed to collect data for scientific studies through questionnaires. We will assess whether children with asthma get bronchodilators (for symptom relief) and maintenance use of ICS (in case of more severe symptoms and less controlled disease) according to (inter) national guidelines [29], and look for differences in proper treatment of asthma between intervention and control group.

### Exacerbation of wheezing

Parents will be asked to register all exacerbations of asthma-like symptoms. This is facilitated by the same mobile application as is used for registration of pharmacotherapy.

### Growth

Weight and height will be assessed in height standard deviation (SD) z-scores according to national growth data. Height velocity will be calculated.

### Asthma or transient wheeze diagnosis at 6 years

The final diagnosis of transient wheeze or asthma will be made by two paediatric pulmonologists after the clinical visit at the age of 6 years. These paediatric pulmonologists will be blinded for the probability diagnosis (if applicable) of the participants. The asthma diagnostic algorithm for children as published by the ERS taskforce in 2021 [38] will be used to establish this final diagnosis. A diagnosis of asthma is made in children with symptoms of asthma when at least two out of the following objective test results are abnormal: spirometry, BDR or FeNO. With respect to spirometry, an FEV_1_/FVC ≤ the lower limit of normal (LLN) or ≤ 80%, ór an FEV_1_ ≤ LLN or ≤ 80% of predicted should be considered abnormal. If this is the case, BDR testing will be performed and an increase in FEV_1_ of more than 12% and/or more than 200 mL following an inhalation of 400 µg salbutamol is considered as an abnormal test result. A FeNO value ≥ 25 ppb should be considered as an abnormal test result. In those patients in which spirometry is normal, but FeNO concentration is higher than 25 ppb, a direct bronchial challenge test using methacholine will be performed. A provocative concentration of methacholine of ≤ 8 ml/mL that results in a 20% drop in FEV_1_ should be considered as a positive test.

Statistical methods

General descriptive statistics will be applied to describe the baseline characteristics. Table 2 depicts the different study groups in which the main statistical analyses will be performed.

**Table 2 Tab2:** outcome parameters and corresponding outcome measures and methods of analysis (see Fig. 5 for corresponding analysis groups)

Outcome	Analysis group	Outcome measure	Methods of analysis

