### Assessment accuracy of the VOC sensing techniques (GC-tof–MS, SIFT-MS)

The primary outcome of the prospective cohort study is assessed in two ways, namely by comparing the VOCs data of the two VOCs-sensing techniques (GC-*tof*–MS and SIFT-MS) at inclusion of all participating children (both wheezing preschool children and healthy controls) to the final diagnosis at six years of age, and by comparing the VOCs-data of the SIFT-MS at the baseline visit to the results of the gold standard (GC-*tof*–MS) at the baseline visit. The sensitivity, specificity, positive predictive value and negative predictive value for a diagnosis of asthma of the two different VOCs sensing techniques (GC-*tof*–MS and SIFT-MS) will be determined with corresponding 95% confidence intervals. Statistical analysis of the volatilome will be performed by current published standards on data analysis for VOCs analysis in breath [51]. The extensive VOCs data derived from the mass spectrometry analyses will be implemented in an algorithm by using mathematical models for analysis of sensor signals (for instance neuronal networks, random forest, support vector machine, or principle component analysis) as described previously [37].

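### The cut-off for a positive methacholine challenge is printed in an impossible unit (8 ml/mL), so as written it excludes no child who shows the required fall in FEV1

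*Protocol article*

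**What the plan says.** The Lung function section lists the tests done at the final visit at age 6. It reserves the challenge for an undecided group: "Only in a subset of patients in which a conclusive asthma diagnosis cannot be made based on spirometry, BDR and FeNO". On how the challenge is done, the section says only that "a direct bronchial challenge test will be performed by administrating aerosols of methacholine". It gives no threshold or unit there.

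The section on the diagnosis at 6 years gives the decision rules. Asthma is diagnosed in a child with symptoms "when at least two out of the following objective test results are abnormal: spirometry, BDR or FeNO". The challenge comes in as a further step: "In those patients in which spirometry is normal, but FeNO concentration is higher than 25 ppb", the child goes on to methacholine. The positivity rule opens with "A provocative concentration of methacholine of", then a less-than-or-equal sign, then "8 ml/mL that results in a 20% drop in" FEV1.

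The same section names its source: "The asthma diagnostic algorithm for children as published by the ERS taskforce in 2021 [38] will be used to establish this final diagnosis".

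The section on the accuracy of the VOC sensing techniques compares the baseline breath data "to the final diagnosis at six years of age", and Table 2 lists this diagnostic value as a primary outcome of the cohort study.

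**The concern.** A provocative concentration is only a decision threshold if some achievable concentrations lie above it and some below. With the printed unit, none can lie above it. The rule then reduces to whether FEV1 fell by 20% at all, and the concentration plays no part.

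At stake is the classification of the challenged children, whose diagnosis the other tests have left open. Methacholine is not one of the three tests in the two-of-three rule, so this sentence is the only place where the article says what a positive challenge is. The diagnosis that results is the standard against which sensitivity, specificity and predictive values of GC-tof-MS and SIFT-MS are calculated, so an error in reading challenges would carry into those estimates.

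**Working it through.** This is a check of units. The plan offers no calculation to reproduce.

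**Inputs, all from the protocol article**
- Threshold: at or below 8 ml/mL, with a 20% drop in FEV1 (diagnosis at 6 years).
- Quantity being limited: a concentration of methacholine (same sentence).
- Other statements of the unit: none. The Lung function section is the only other place that mentions the challenge, and it gives no figure.

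**Step 1: reduce the unit.** 8 ml/mL = 8 mL ÷ 1 mL = 8, a pure number, or 800% by volume.

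**Step 2: compare with what is possible.** Let c be the volume of solute per volume of solution. The solute is part of the solution, so 0 ≤ c ≤ 1. The printed limit is 8 times the largest possible value. A volume ratio can be a legitimate way to state a concentration; what makes this one impossible is the value of 8.

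**Step 3: apply the rule literally.** Positive = (20% fall in FEV1 at concentration c) and (c ≤ 8). Since c ≤ 1 < 8 always, the second condition is always true. The rule becomes: positive = 20% fall at any concentration.

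**Step 4: trace where the result goes.**

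| Part of the plan | Depends on the challenge threshold? |
|---|---|
| Two-of-three rule (spirometry, BDR, FeNO) | No |
| Final diagnosis of children who are challenged | Yes |
| Accuracy of GC-tof-MS and SIFT-MS against the final diagnosis | Yes, through those children |
| RCT primary outcome (TRACK) | No |
| RCT sample size and alpha | No |

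**Step 5: can the effect be sized?** No. The article gives no expected number of challenged children and describes the group in two ways: no conclusive diagnosis after spirometry, BDR and FeNO, or normal spirometry with FeNO above 25 ppb. Without that number, and without knowing which unit the centres use, no shift in sensitivity or specificity can be calculated.

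**The case against.** The strongest reply is that nobody will apply the printed unit. The article says that a named published algorithm will be used for the final diagnosis, that SOPs go to all sites, that study personnel are trained, that the CRF metadata hold the units, and that two paediatric pulmonologists make the diagnosis. The right unit is probably in those sources, and this sentence is probably a slip of typing.

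Most of that stands. It means that the literal consequence in step 3 shows that the printed rule fails, and does not predict what will happen in the trial. It does not make the sentence right: the article states a threshold, states it wrongly, and can be corrected only from sources outside it. Nor does it look like damage from reading the PDF, since mL, µg and ppb are intact in the same section.

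Three stronger readings are tempting and are not supported.
- A reader might infer a dosing hazard. The 8 is a cut-off for interpreting a result, and is not an instruction on what to administer.
- A reader might object that the concentration steps and top concentration are missing. A journal article commonly leaves such procedure to the full protocol or SOP.
- A reader might infer that the whole age-6 diagnosis is undefined. The two-of-three rule does not use methacholine, and the challenge is done only in a subset.

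**Conclusion.** The concern holds in a limited form. The printed threshold is impossible as a volume ratio, excludes no child with a 20% fall in FEV1, and is not corrected anywhere else in the article. It is the only stated criterion for a positive challenge.

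Its reach is the final diagnosis of the challenged subset and, through them, the cohort analyses that use that diagnosis as reference standard. The RCT primary outcome is untouched. Analysis groups II to IV in Table 2 are defined in a figure that is not available here, so I make no claim about the secondary comparisons in those groups.

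The conclusion that the text is wrong needs only the unit as printed. That it is a misprint, and that the algorithm, SOP and CRF carry a usable unit, are assumptions, because none of those sources is at hand. If they do, the practical effect is nil beyond the wording. If the misprint was copied into the SOP or CRF, challenge results could be recorded or read differently between centres. The documents do not show which is the case, and that is reason enough for a check.

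**What to change.** 1. Reconcile the unit of the threshold in the section on the diagnosis at 6 years with the cited algorithm (reference 38) and the lung-function SOP. The unit should come from those sources; none is proposed here.
2. Restate the positivity rule in that unit.
3. Confirm that the CRF field and its metadata carry the same unit, and that all measurement centres report the provocative concentration in it.
4. If any challenge result has already been entered, check its recorded unit before the final diagnoses are used in the accuracy analysis.

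The cost is one line of protocol wording and a short check of the SOP and CRF. Sample size, visits and the analysis of the RCT primary outcome do not change.
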